## Abstract

**Supplementary Information:**

The online version contains supplementary material available at 10.1186/s13063-021-05682-y.

## Introduction

The development of rheumatoid arthritis (RA) and osteoarthritis (OA) have been linked to diet and obesity [1–8]. Studies indicate fasting, a Mediterranean diet, as well as a whole food plant-based diet (WFPD) can lower disease activity in patients with RA [9–14]. In OA, hypocaloric and WFPDs showed favorable results, while the effect of a hypocaloric diet in combination with exercise was superior, suggesting synergies for multidisciplinary interventions [15–18].

For exercise, it has been shown that physical activity is associated with a lower risk of RA [19]. In patients with RA, long-term high-intensity exercise is effective in improving functional and emotional status [20]. Routinely combining aerobic exercise with muscle strength training (similar to the Dutch Exercise Guideline) is recommended for patients with RA [21]. Additionally, for patients with OA in the hip and/or the knee, exercise improves physical function and lowers pain [16, 17].

For both RA patients and patients at increased risk for RA, the heart rate is controlled increasingly by the sympathetic nervous system in contrast to the parasympathetic nervous system. This results in a lower heart rate variability suggesting a higher level of stress [22, 23]. The onset of RA has also been linked to stress [6, 7, 24], and both Mindfulness Based Stress Reduction (MBSR) as well as internet-based cognitive-behavioral therapy have shown favorable outcomes, especially with regard to general wellbeing [25, 26]. For OA, a small pilot study showed a significant reduction of pain and improvement of function in patients who followed an 8-week meditation program. In OA patients, higher baseline “mindfulness” scores were also associated with a better response to exercise than patients with lower baseline mindfulness, suggesting again the synergistic effects of combining more disciplines within one intervention [27].

A multidisciplinary program based on a WFPD, exercise, and stress management showed favorable results for patients with coronary artery disease [28]. Although the separate components of this multidisciplinary lifestyle intervention were found to be beneficial for RA and OA patients, no studies have yet been conducted to investigate the effect of an integrated program for RA or OA.

The presence of low-grade inflammation is a feature of many chronic diseases including RA and OA [29]. In RA, a chronic autoimmune arthritis condition, the presence of low-grade inflammation—possibly intermediated by microbiome dysbiosis—may cause the breakdown of immune tolerance [29, 30]. Support for the mucosal origin of RA comes from the observation that part of the circulating RA-associated autoantibodies rheumatoid factor (RF) and anti-citrullinated protein antibodies (ACPA) are of mucosal origin [30]. Additionally, compared to healthy individuals, an altered, or dysbiotic, microbiome is seen in RA and its preclinical stage, with, among others, an overrepresentation of *Lactobacillus salivarius* and *Prevotella copri* [31]. As the microbiome is affected among others by diet, exercise, and stress, these lifestyle factors may therefore contribute to the pathogenesis of RA at mucosal sites [30–33].

Low-grade inflammation is also associated with metabolic syndrome, a combination of risk factors such as high fat mass (waist circumference), high blood pressure, high low-density lipoprotein (LDL), low high-density lipoprotein (HDL), high triglycerides, and high fasting glucose, which are very common in patients with OA [29, 34]. Levels of inflammatory mediators are higher in people with visceral adiposity, which may mediate the relationship between OA and obesity [35]. This has resulted in the denomination of metabolic syndrome-associated osteoarthritis (MSOA) as a specific form of OA [36]. MSOA is a chronic condition with limited treatment options (analgesics, nonsteroidal anti-inflammatory drugs (NSAIDs), and intra-articular glucocorticoids), and although guidelines for the treatment of OA also recommend exercise treatment, weight loss, and mental health interventions, they also emphasize the need for more studies, especially regarding multidisciplinary interventions.

The systemic impact of low-grade inflammation, microbiome dysbiosis, and increased (mostly visceral) fat mass also explains the frequent occurrence of comorbidities, such as diabetes and cardiovascular disease in patients with OA and RA [34, 37].

### Research objective

The objective of Plants for Joints is to study the effects of a multidisciplinary lifestyle program in patients with (risk for) RA and in patients with MSOA. The program consists of a WFPD, exercise, and stress management and aims to lower disease activity in patients with RA (randomized controlled trial [RCT] 1), to lower the risk of RA [38] in patients with ACPA-positive arthralgia (RCT 2), or to improve the scores for pain, stiffness and function in patients with MSOA (RCT 3), all in comparison to usual care. An observational extension study is added to investigate adherence.

## Design and methods

### Design

We designed three 16-week observer-blind RCTs with a waiting-list control group for patients with RA (RCT1), for patients at risk for RA, defined by ACPA-positive arthralgia (RCT 2) and for patients with MSOA (RCT 3) [39]. All participants receive the program, either directly or after participation in the control group.

Medication for RA is kept stable during the RCT (16 weeks for the intervention group, 32 weeks for the control group) whenever possible. DMARD changes (in RA patients) and intercurrent corticosteroid administration is considered a protocol deviation and the reason for the change will be registered.

In a 2-year extension study, starting at the end of the 16-week lifestyle program, all patients receive continued online support and 6 additional, thematic and facultative meetings. During the extension study, we will investigate adherence to the lifestyle program in relation to long-term effects and success factors for and barriers to changing behavior.

Study visits are at baseline, 8 and 16 weeks during the RCT, at 8 and 16 weeks for the waiting-list control group after entering the intervention, and every 6 months during the extension period.

A schedule of the intervention and the measurements during the 16-week RCT is shown in Fig. 1. Figure 2 shows a comprehensive scheme based on the SPIRIT format and includes the intervention phase for the waiting-list control group and the 2-year extension study. The SPIRIT Checklist is available as an additional file (supplement 1) [39].

**Fig. 1 Fig1:**
[figure not shown]
Schedule of intervention and measurements during the randomized controlled trial (RCT). DAS28, disease activity score based on 28 joints; RA, rheumatoid arthritis; HRV, heart rate variability; DEXA, dual-energy x-ray absorptiometry; MRI, magnetic resonance imaging

**Fig. 2 Fig2:**
[figure not shown]
SPIRIT figure with phases of the study and data collection time points. (X) = measurement only for waiting-list control group. RCT, randomized controlled trial; yr, year; ext, extension; DAS28, disease activity score based on 28 joints; WOMAC, Western Ontario and McMaster Universities Osteoarthritis Index; RA, rheumatoid arthritis; PROMIS®, Patient Reported Outcomes Measurement Information System; DEXA, dual-energy x-ray absorptiometry; LDL, low-density lipoprotein; HDL, high-density lipoprotein; ESR, erythrocyte sedimentation rate; HbA1c, hemoglobin A1c; MRI, magnetic resonance imaging; HRV, heart rate variability; EQ-5D-5L, EuroQol 5 dimensions 5 levels

### Recruitment, selection, and randomization of participants

Subjects aged ≥ 18 years are recruited through rheumatologists, rehabilitation specialists, nurses and allied health care professionals at Reade and Amsterdam UMC (The Netherlands), and other regional hospitals or health centers. The main inclusion criteria are as follows: (RCT 1) RA according to the American College of Rheumatology (ACR)/European Alliance of Associations for Rheumatology (EULAR) 2010 criteria [40] with low to moderate disease activity (2.6 ≤ DAS28 ≤ 5.1) [41] and unchanged use of disease-modifying anti-rheumatic drugs (DMARDs) for 3 months or non-use of DMARDs; (RCT 2) arthralgia and positivity for ACPA [38]; and (RCT 3) OA in hip and/or knee, diagnosed according to the clinical criteria of the ACR (without age-criterion) [42, 43] and metabolic syndrome according to the criteria defined by the National Cholesterol Education Program (NCEP) Adult Treatment Panel III (ATP III) [44]. The main exclusion criteria are as follows: insufficient e-health competencies to fill in digital questionnaires and keep an online food diary, already following a predominantly plant-based diet, underweight (BMI < 18.5 kg/m^2^), pregnancy, and unwillingness to stop smoking for at least the duration of the RCT, if applicable.

The study has a parallel trial design in which patients are randomized in a 1:1 ratio by the researchers using CASTOR (an electronic database platform for data collection, management, and storage, with strictly defined user roles and patient management procedures, which keeps an audit trail) with a variable block randomization in block sizes of 2 and 4 (not stratified).

Both patients as well as study staff are not blinded for allocation. During measurements, a research nurse or other researcher, not involved in the study and not aware of allocation or phase of the study, will execute the examination for DAS28 (physical examination of the joints). Other primary and secondary outcomes are blinded by default (automized questionnaires or laboratory markers).

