### Sample size calculation

Based on *α* = 0.05 and power (1-β) = 0.80, effects ranged from 0.4 to 1.0 decreases for the DAS28 (estimated from component data of the DAS28 in the case of the trial by Kjeldsen Kragh et al.) with standard deviations (SD) ranging from 0.6–1.0 [12, 14]. The minimal clinically important improvement (MCII) in the DAS28, however, increases with higher baseline values and vice versa [60]. In the range of our inclusion criterion of DAS28 (between 2.6 and 5.1), the MCII is 0.8. Sköldstam et al. reported a difference in the DAS28 of 0.5 in 12 weeks [14]. In our 16-week study, we expect an additional effect on top of that provided by diet alone, due to the combination with exercise and stress management. Based on clinically relevant effect sizes of delta 0.8 with a SD of 1.2 for the DAS28, *α* of 0.05, and *β* of 0.2, we need a sample size of 56.

For OA patients, we found effects ranging from 2.2 to 2.8 for WOMAC pain (OA) and 5.7 to 10 for WOMAC function (OA) and standard deviations (SD) ranging from 0.4 to 0.6 with an exceptional 3.1 for WOMAC pain and 1.4 to 3.1 with an exceptional 10.9 for WOMAC function [15, 61, 62]. Based on these studies, we estimated that a power of 0.80 is feasible with a total of 60–70 subjects (intervention + control group) and planned to aim for 80 subjects for both RA as well as OA patients (total 160 patients) based on a possible dropout rate of approximately 20%.

For patients with ACPA-positive arthralgia, we added a pilot group of 16 participants (*n* = 8 intervention group, *n* = 8 waiting-list control group).

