## Trial status

Patient recruitment began in May 2019. The trial is currently underway. Article based on protocol version 7.0 (March 2021). Recruitment of patients is expected to be completed in August 2021.

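### Unblinded researchers randomise in blocks of 2 and 4, which weakens allocation concealment and creates an avoidable risk of selection bias at enrolment

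*Protocol article*

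**What the plan says.** The section on recruitment, selection and randomization fixes three things together:

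- Who randomises, and how: "patients are randomized in a 1:1 ratio by the researchers using CASTOR".
- The scheme: "with a variable block randomization in block sizes of 2 and 4 (not stratified").
- Blinding: "Both patients as well as study staff are not blinded for allocation".

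The section describes CASTOR as a platform "with strictly defined user roles and patient management procedures, which keeps an audit trail". It does not say who can see the block sizes, whether the person who randomises also judges eligibility, or whether each RCT has its own list. Patients are "recruited through rheumatologists, rehabilitation specialists, nurses and allied health care professionals" at several institutions.

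The scheme is stated once for the whole study, so it covers all three RCTs. For RCT 1 and RCT 3 the sponsor "planned to aim for 80 subjects for both RA as well as OA patients"; for RCT 2, "we added a pilot group of 16 participants". The primary model in the Statistical analysis section adjusts for the baseline value of the outcome. On timing, the Trial status section says: "Recruitment of patients is expected to be completed in August 2021".

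**The concern.** An electronic list hides future allocations only if they cannot be worked out from past ones. In an open trial the past ones are visible to unblinded staff. With blocks of 2 and 4, the running difference between arms never exceeds 2 and returns to zero within four patients. Guessing the arm that is behind therefore works well, even for someone who does not know which block size is in use.

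A person who expects the next slot to be intervention could, knowingly or not, enrol a different kind of patient or time an enrolment accordingly. The entry criteria leave some room for discretion, for example in judging e-health competence and willingness to stop smoking. Selection on factors that the baseline score does not capture would pass into the treatment comparison. The blinded joint examination for the DAS28 protects measurement, not enrolment.

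**Working it through.** The plan gives no predictability figure, so there is none to reproduce.

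**Inputs.** From the document: block sizes 2 and 4, 1:1 allocation, unblinded staff, 80 patients in each of RCT 1 and RCT 3, 16 in RCT 2, and the SD of 1.2 and difference of 0.8 for the DAS28 (Sample size calculation section). Assumed: the two sizes are equally likely, with 25% to 75% blocks of 4 as the range.

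**Guessing rule.** Guess the arm that is behind; toss a coin when the arms are level.

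*Block of 2.* The first allocation is a coin toss (0.5) and the second is determined (1). Expected correct: 1.5 of 2. One allocation is made with the arms unequal, and that guess is always right.

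*Block of 4.*
- First: coin toss, 0.5.
- Second: the arm behind comes up with probability 2/3.
- Third: level with probability 2/3 (coin toss), otherwise determined: 2/3 × 0.5 + 1/3 × 1 = 0.667.
- Fourth: determined, 1.

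Expected correct: 0.5 + 0.667 + 0.667 + 1 = 2.833 of 4. Allocations made with the arms unequal: 1 + 1/3 + 1 = 2.333, of which 2/3 + 1/3 + 1 = 2 are guessed correctly.

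*Equal mix, per 6 allocations on average.*
- Correct guesses: (1.5 + 2.833)/6 = 13/18 = 72.2% (range 71.4% to 73.3%), against 50% by chance.
- Guessable better than chance: (1 + 2.333)/6 = 5/9 = 55.6% (range 53% to 57%).
- Accuracy on those: (1 + 2)/3.333 = 90% (range 87.5% to 93.8%).
- Coin tosses: 1 − 5/9 = 44.4%.
- Certain, current block size hidden: only when one arm leads by 2, which happens in 1/3 of blocks of 4 and fixes two allocations: (2 × 1/3)/6 = 11.1%. Simulation of a guesser who knows the sizes and all past allocations but not the current block gave 10.4% at N = 16 and 11.0% at N = 80.
- Certain, each block size known: (1 + 1.333)/6 = 7/18 = 38.9%.

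**Possible bias.** Suppose prognosis is shifted by +η when intervention is guessed, by −η when control is guessed, and not at all when the arms are level. With p the correct-guess rate, the expected difference between arms is 2η(2p − 1) = 2η(2 × 0.7222 − 1) = 0.89η. The document gives no η. For illustration, at SD 1.2:
- η = 0.05 SD: 0.89 × 0.05 × 1.2 = 0.05 DAS28 units.
- η = 0.10 SD: 0.89 × 0.10 × 1.2 = 0.11 DAS28 units, or 13% of the planned 0.8.

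**Other block sizes** (the last two figures in each row simulated at N = 80; the rest enumerated, equal mix):

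| Blocks | Correct guesses | Bias multiplier of η | Guessable at 80% or better | Certain |
|---|---|---|---|---|
| 2, 4 | 72% | 0.89 | 55% | 11% |
| 4, 6 | 69% | 0.77 | 27% | 6% |
| 4, 6, 8 | 68% | 0.72 | 24% | 2% |

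At η = 0.10 SD, blocks of 4, 6 and 8 lower the illustrative bias from 0.107 to 0.72 × 0.10 × 1.2 = 0.087 DAS28 units.

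**The case against.** Several counter-arguments stand.

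- **Access and behaviour are not documented.** Exploiting the scheme requires the person who decides on enrolment to see the running allocations on that list, to track them and, for the stronger predictions, to know the sizes. Referring clinicians at other institutions may see none of this. That researchers operate CASTOR does not show that they judge eligibility. User roles and the audit trail help to protect the list, though they cannot hide past allocations from unblinded researchers.
- **A reader might infer that most allocations are predictable.** That holds only in the sense of a slight majority being guessable better than chance. Only about 11% are certain with the block size hidden, and 44% cannot be guessed at all.
- **A reader might take the remark on motivation in the Limitations section as support for bias between arms.** That remark is about generalising the findings. It describes participants in both arms and says nothing about selection by expected allocation.
- **The bias figures are scenarios.** η has no source in the document, an η of 0.1 SD is really a contrast of 0.2 SD between guessed arms, and the formula applies it to every guessable patient.
- **Larger blocks are a partial remedy, and late.** Correct guesses fall by only four percentage points, and recruitment was close to its expected end.

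The timing limits the block change to the remaining patients. It does not affect an analysis check, which can still cover everyone.

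**Conclusion.** The point holds as a design weakness. The stated combination of researcher-run randomisation, open allocation and the two smallest block sizes leaves a 72% correct-guess rate to anyone who follows the list, and varying between 2 and 4 protects little. That rate rests on assumed mixing but moves only between 71% and 73% over the range tested.

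The size of any bias is unknown: about 0.89η, or roughly 0.05 to 0.11 DAS28 units if η lies between 0.05 and 0.1 SD. The document does not support a claim that the three RCTs are biased. Nor does it show that eligibility and baseline data were left open until allocation was released; an article commonly leaves that detail to the full protocol, so its absence here is no finding.

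**What to change.** **Patients still to be randomised.** Drop block size 2 and use larger, randomly chosen blocks, for example 4, 6 and 8, with 4 and 6 in the 16-patient RCT 2. Withhold the sizes from enrolling staff. The gain is mainly in strong predictions: with 4, 6 and 8, those at 80% or better fall from about 55% to 24%, and certain ones from 11% to 2%.

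**Patients already randomised.** Reconstruct the allocation order from CASTOR and compute, for each patient, the probability of intervention given the earlier allocations on that list. Regress the baseline score on this probability, and add it as a covariate next to group in the primary model (a Berger-Exner-type analysis). Report this as a sensitivity analysis in RCT 1 and RCT 3. In RCT 2 keep it descriptive, since 16 patients can show very little.

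**Reporting.** State who had access to running allocations and block sizes, and whether those people decided on enrolment.

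**Cost.** A change of settings, one extra analysis with limited power, and no extra patients. The possible difference in arm sizes within an open block rises from at most 2 to at most 4 with blocks of 8, or 3 with blocks of 6.

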#### Secondary outcome measures

Secondary outcomes are the same for all groups in the three RCTs: RA, ACPA-positive arthralgia, and MSOA, unless otherwise specified. Quality of life-related outcomes measured are self-reported physical, mental and, social health, using the validated Dutch-Flemish Patient Reported Outcomes Measurement Information System (PROMIS®) [53]. In order to select the most important secondary patient reported outcomes, we consulted the *Ambassadors*. From a list of 13 physical, mental and social item banks (see supplement 5), they chose physical function, fatigue, and pain interference as most important. We added depression to this list, since it is strongly associated with the onset of RA [7, 24]. Other secondary outcomes are waist circumference, fat mass (measured by dual-energy X-ray absorptiometry [DEXA]), blood pressure, LDL, HDL, triglycerides, fasting glucose, and ESR.

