### Statistical analysis

At baseline, half-way (8 weeks) and at the end of the study (16 weeks) outcomes are measured (see supplement 5 for a specification of the measurements).

After conclusion of the randomized controlled trial, data will be cleaned, verified by two researchers, and inspected for errors, inconsistencies, and incomplete information. Outliers will be inspected and corrected if necessary.

Primary outcomes DAS28, RA risk-scores, and WOMAC (all continuous variables) at 8 and 16 weeks in the intervention group will be compared with outcomes at 8 and 16 weeks in the control group, adjusted for baseline scores. Intention-to-treat analyses will be performed, with additional per-protocol analyses. For the analyses, a repeated measures mixed model will be used with random effect for the subjects and fixed effects for group (intervention or control) and baseline values for DAS28, RA risk-score, or WOMAC.

Secondary outcome measures (physical function, fatigue, pain interference, depression, waist circumference, fat mass, blood pressure, LDL, HDL, triglycerides, fasting glucose and ESR) will be analyzed the same way as the primary outcomes. Statistical tests will be limited to primary and secondary outcomes. For other outcomes, descriptive statistics will be used. We will analyze microbiome, remaining metabolic and stress-related outcomes separately and report results in dedicated articles.

In the extension study, the primary and secondary outcomes of the intervention study will become secondary outcomes, and adherence will be the primary outcome. These outcomes are analyzed in the same way as the intervention study, using the baseline, halfway, and end measurements from the 16-week intervention program, as well as 6-, 12-, and 18-month and end (24 month) measurements of the extension study. Intention-to-treat analyses will be performed, with additional per-protocol analyses. Since the extension study is observational, a within-subject analysis will be performed using a repeated measures mixed model with random effect for the subjects and fixed effects for baseline values.

*P* values < 0.05 will be considered to be significant.

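### The article counts every outcome outside the DAS28 joint examination as inherently blinded, which is wrong for three of the 12 tested secondary outcomes: waist circumference, blood pressure and DEXA fat mass

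*Protocol article*

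**What the plan says.** The blinding paragraph of the protocol article (Recruitment, selection, and randomization of participants) makes three statements in sequence.

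- On patients and staff: "Both patients as well as study staff are not blinded for allocation".
- On the one blind observer, someone from outside the study: "not aware of allocation or phase of the study, will execute the examination for DAS28 (physical examination of the joints"). The article gives this person no other task.
- On everything else: "Other primary and secondary outcomes are blinded by default (automized questionnaires or laboratory markers").

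Secondary outcome measures names four PROMIS domains and then continues: "Other secondary outcomes are waist circumference, fat mass (measured by dual-energy X-ray absorptiometry [DEXA]), blood pressure, LDL, HDL, triglycerides, fasting glucose, and ESR". Under Statistical analysis, the secondary outcomes "will be analyzed the same way as the primary outcomes", and "Statistical tests will be limited to primary and secondary outcomes". The threshold is given as P "values < 0.05 will be considered to be significant". The Design section describes all three trials as observer-blind.

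**The concern.** The point concerns the observer, not the patient who fills in a questionnaire. The article gives a reason why no observer blinding is needed outside the joint examination: what remains is collected automatically or in a laboratory. Its own outcome list contains measurements made on the patient's body, to which that reason does not apply.

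The claim of blinding affects how results are read. Waist circumference and blood pressure are among the metabolic syndrome components named in the Introduction, and metabolic syndrome is an entry criterion for RCT 3. The programme promotes weight loss in overweight patients, so an observer who knew the arm would expect a smaller waist in the intervention group. If such expectation shifted the readings, the shift would appear as a treatment effect on a formally tested outcome. A reader relying on the article would believe that the design had excluded this.

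**Working it through.** **Classification check.** No published figure underlies the sentence, so the check sets the blinding paragraph against the list of secondary outcomes under Statistical analysis.

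| Type | Outcomes | Count |
|---|---|---|
| Questionnaire | physical function, fatigue, pain interference, depression | 4 |
| Laboratory marker | LDL, HDL, triglycerides, fasting glucose, ESR | 5 |
| Neither | waist circumference, fat mass by DEXA, blood pressure | 3 |
| Total | | 12 |

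The stated reason for blinding therefore fails for 3 of 12 tested secondary outcomes. It does not fail for any primary outcome through this route: the DAS28 joint counts have the blind assessor and ESR is a laboratory value, while the WOMAC is a questionnaire.

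**Who measures.** Study staff are unblinded, and the blind assessor's only stated task is the joint examination. Together these suggest that unblinded staff take waist and blood pressure. No sentence says so.

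**Illustration of sensitivity.** Every input below except the sample size is an assumption.

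- Sample size: 80 planned per trial in RCTs 1 and 3, less about 20% dropout (Sample size calculation), gives 80 × 0.8 = 64, or 32 per arm.
- Assumed: waist SD 12 cm with baseline correlation r of 0.8–0.9; systolic pressure SD 15 mmHg with r of 0.6–0.7; a differential observer error b between arms.
- Formulas: SE = SD × √(1 − r²) × √(2/n). False-positive rate = P(|Z + b/SE| > 1.96), with Z standard normal and no true effect.
- Waist, r = 0.8: 12 × 0.600 × 0.25 = 1.80 cm. Waist, r = 0.9: 12 × 0.436 × 0.25 = 1.31 cm.
- Systolic pressure, r = 0.6: 15 × 0.800 × 0.25 = 3.00 mmHg. Systolic pressure, r = 0.7: 15 × 0.714 × 0.25 = 2.68 mmHg.

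| Outcome | Assumed error b | b/SE | False-positive rate |
|---|---|---|---|
| Waist | 1 cm | 0.56–0.76 | 8.6–11.9% |
| Waist | 2 cm | 1.11–1.53 | 19.9–33.4% |
| Systolic pressure | 2 mmHg | 0.67–0.75 | 10.2–11.6% |
| Systolic pressure | 3 mmHg | 1.00–1.12 | 17.0–20.2% |

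These rates do not carry over to RCT 2. With 8 per arm, even before any dropout, the waist SE is 2.6–3.6 cm. A 1 cm error then gives about 6–7% and a 2 cm error about 9–12%. The formula also treats one time point, whereas the plan uses a repeated measures model over 8 and 16 weeks.

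**The case against.** The strongest reply is that the article never says unblinded staff take these measurements. It does not say that the blind assessor does the joint examination and nothing else, and it refers measurement details to supplement 5, which is not shown. Who holds the tape and which device is used are details that an article may leave to the full protocol. Blood pressure may be taken by an automatic device, and DEXA is an instrument reading. The article is also open about unblinded patients and staff, and no primary outcome is affected.

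Most of this stands. A reader might infer that waist and blood pressure are in fact measured by people who know the arm, and that the results are therefore biased. The documents do not support that as a fact: neither measurer nor device is stated, and the false-positive rates show only what an error of a given size would do. A reader might also extend the point to grip strength and the get-up-and-go test. Those are listed under Other outcome measures, receive only descriptive statistics, and were never said to be blinded.

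What the reply does not remove is the sentence itself. It is a positive statement, not an omission, and the article's own outcome list contradicts it. Even if supplement 5 named a blind measurer, the reason given in the article would still be wrong for these three outcomes.

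**Conclusion.** The concern holds as a misstatement about blinding. The article treats all primary and secondary outcomes outside the joint examination as blinded by their nature, and this is untrue for 3 of the 12 formally tested secondary outcomes. Measurement by unblinded staff is an inference from the stated roles. If it is correct, the risk of observer bias is clearest for tape-measured waist, depends on the device for blood pressure, and is small for DEXA fat mass. The false-positive figures are illustrative, rest on assumed SDs, correlations and differential errors, and apply at most to RCTs 1 and 3. The DAS28 joint counts, the laboratory outcomes and the sample size are not touched.

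**What to change.** 1. Correct the parenthesis in the blinding paragraph so that waist circumference, blood pressure and DEXA fat mass are no longer presented as blinded by default.
2. At RA visits, where the blind DAS28 assessor is already present, have that person also take waist circumference and blood pressure, without sight of earlier values.
3. At all other visits, and for visits already held without a blind measurer, report these outcomes as not observer-blinded and interpret their P values accordingly.

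The cost is a wording change and a few more minutes of an assessor who is already at the RA visits. The downside is that the stated blinding becomes less favourable. A blind measurer at the MSOA visits is not part of this fix: the article ties the DAS28 to RCT 1 and mentions no joint-count assessor for RCT 3, so that would need extra staff. Recruitment began in May 2019 and was expected to finish in August 2021 (Trial status), so for many visits only the change in reporting remains possible.
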